## List of abbreviations

|         |                                                                   |
|---------|-------------------------------------------------------------------|
| AGP     | Alpha-acid-glycoprotein                                           |
| APP     | Acute phase protein                                               |
| BIA     | Bioelectrical impedance analysis                                  |
| CIOMS   | The Council for International Organizations of Medical Sciences   |
| CRP     | C-reactive protein                                                |
| CSB     | Corn Soy Blend                                                    |
| CSPS    | Centre de Santé et de Promotion Sociale                           |
| CRF     | Case-report form                                                  |
| DSM     | Dry Skimmed Milk                                                  |
| EFA     | Essential fatty acids                                             |
| FAO     | The Food and Agriculture Organization of the United Nations       |
| FBF     | Fortified Blended Flours                                          |
| FGD     | Focus Group Discussion                                            |
| IAEA    | International Atomic Energy Agency                                |
| ICH-GCP | International Conference on Harmonisation- Good Clinical Practice |
| iCSBS   | Improved Corn Soy Blend Supplement                                |
| IGF-1   | Insulin-like Growth Factor 1                                      |
| IRSS    | Institut de Recherche en Sciences de la Santé, Burkina Faso       |
| LNS     | Lipid-based Nutritional Supplement                                |
| MAM     | Moderate Acute Malnutrition                                       |
| MSF     | Médecins sans Frontières                                          |
| MUAC    | Mid Upper Arm Circumference                                       |
| RCT     | Randomized Controlled Trial                                       |
| RUTF    | Ready-To-Use-Therapeutic Food                                     |
| Science | The Faculty of Science, University of Copenhagen                  |
| SAM     | Severe Acute Malnutrition                                         |
| TBW     | Total Body Water                                                  |
| UNHCR   | United Nations High Commissioner for Refugees                     |
| UNICEF  | United Nations Children's Fund                                    |
| WFP     | World Food Program                                                |
| WHO     | World Health Organization                                         |
| WHZ     | Weight-for-Height Z-score                                         |

## Summary

### Background

Moderate acute child malnutrition (MAM) is a major global health problem, affecting about 36 million children worldwide. There is no consensus on how to manage children suffering from MAM. Children have typically been given fortified blended flours, such as corn-soy blend (CSB), a product developed more than 30 years ago. More recently the limitations of CSB have been recognized and WFP has developed and is currently introducing improved CSBs called CSB+ and CSB++. Other organizations are also currently developing and testing various products for the management of MAM, including lipid based nutrient supplements. However there is no consensus on the most suitable product. Therefore there is a crucial need to develop and evaluate specific interventions for children suffering from MAM.

New food products should be tested using outcome measures of importance for body function, rather than just increase in weight. Increase in weight may simply be due to accumulation of fat and therefore not providing a long-term benefit to the child. Randomized trials with lean body mass (LBM) as the primary outcome and functional measures as secondary outcomes are needed to identify new cost-effective food supplements for MAM management.

### Objective

Twelve investigational food supplements will be developed, including six improved corn-soy-blend based supplements (iCSBS) and six Lipid based Nutrient Supplements (LNS) combining different soy qualities (dehulled soy, soy isolate) and different amounts of total protein (0%, 20% or 50%) provided by dry skimmed milk (DSM).

This trial aims to assess the effectiveness of a 3 month supplementation with these newly developed products for the management of children 6-23 months old with MAM in Burkina Faso. Effectiveness will be assessed by determining their effects on accrual of lean body mass (primary outcome), linear growth, physical activity, motor milestones, morbidity, hemoglobin concentration, serum acute phase proteins, IGF-1, serum ferritin, serum

---

 The deuterium dilution technique is recommended as the technique of choice to measure the lean body mass in infants and young children (*Wells et al, 2006 & 2009, IAEA*). The technique consists in giving water labeled with deuterium (a stable, naturally-occurring isotope of hydrogen) and to measure, after equilibration, the contents of deuterium in a saliva sample. This measurement allows estimating the total body water (TBW). With the estimation of the TBW, it is possible to estimate the amount of LBM from the hydration of the fat free mass (*IAEA*).

 0%, 20% and 50% of total protein provided by DSM corresponds to 0%, 8% and 20% of total weight.

transferrin receptor, retinol binding protein, whole blood concentrations of essential fatty acids (secondary outcomes) and thymus size. Their respective acceptability will also be assessed.

## **Methods**

### Trial setting and period

This trial will be carried out in five Centres de Santé et de Promotion Sociale (CSPS) supported by ALIMA in the province of Passoré in the northern part of Burkina Faso. The trial is expected to begin in August 2013. The trial has been preceded by a pilot study in February 2013 aiming to test all tools and procedures, to evaluate the acceptability of the experimental foods and to explore perceptions, knowledge and beliefs of caretakers about malnutrition. Formative research about diets and feeding practices and food availability has also been carried out during the pilot in order to adapt locally available nutrition education materials..

### Participants

All children arriving spontaneously at the CSPS program sites will be screened for eligibility. Furthermore active screening will be done in the villages by community health workers supervised by ALIMA. Children will be eligible for inclusion if they fulfil the following criteria:

- 6-23 months of age
- weight-for-height z-score (WHZ)  $\geq -3$  and  $< -2$  (WHO growth standard) or
- MUAC  $\geq 115$ mm and  $< 125$  mm,
- resident in the catchment area at the time of inclusion,
- whose parents/guardians consented to participate.

Children suffering from or having received treatment for severe acute malnutrition (WHZ  $< -3$ , mid-upper-arm circumference  $< 115$  mm, oedema) in the last two months, children with medical complications requiring hospitalization or having been hospitalized in the last two months and children with known allergy to milk, peanut, CSB and/or RUTF will be excluded.

### Trial design

The study consists of a randomized controlled trial of 12 parallel groups each. In total, 1608 eligible children will be included, 134 in each of the 12 intervention groups.

---

 A local calendar of events will be piloted. If it does not appear suitable for inclusion based on age, children would be included based on a combination of event calendar and height.

Figure 1. Trial Design

|          |                         | Dry skimmed milk (% mass / %protein) |       |        |    |
|----------|-------------------------|--------------------------------------|-------|--------|----|
|          |                         | 0%                                   | 8/20% | 20/50% |    |
| R | CSB/Dehulled soy | a                                    | b     | c      | 1. |
|          | CSB/Soy isolate  | d                                    | e     | f      |    |
|          |                         |                                      |       |        |    |
|          | LNS/Dehulled soy | g                                    | h     | i      | 2. |
|          | LNS/Soy isolate  | j                                    | k     | l      |    |

### Interventions

The intervention will last for three months, with an additional three months of follow up. Children will be individually randomized to either: 1) newly developed iCSBS (500 kcal daily for 3 months); or 2) newly developed LNS (500 kcal daily for 3 months). In each of the iCSBS and LNS arms, children will be further randomized to a supplement based on dehulled soy or soy isolate and containing either 0%, 20% or 50% of total protein provided by DSM.

In addition, all groups will receive health and nutritional education and a fortnightly medical evaluation for the three months of intervention and monthly medical evaluation during the three months of follow-up. Children that have not recovered from MAM after 3 months of intervention or who are losing more than 5% of their weight from admission on two consecutive visits will be referred for medical evaluation at Yako Hospital.

### Outcomes

**Primary outcome:** absolute lean mass increment from baseline to 3 months (deuterium dilution method). **Secondary outcomes:** increase of WHZ to >-2, linear growth, increase in MUAC > 125 mm, physical activity, motor and language milestones development, morbidity, level of hemoglobin, serum acute phase proteins, insulin-like growth factor-1, serum ferritin, thymus size and essential fatty acids, acceptability of and adherence to the products.

 That is, children who did not reach a WHZ  $\geq -2$  or a 15% weight increase if admitted with a MUAC  $\geq 115$ mm et < 125 mm

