#### *Secondary objectives:*

- To assess the effectiveness of a 3 month supplementation with newly developed iCSBs and LNS on weight-for-height increase, increase in MUAC, linear growth, thymic size, physical activity, child motor and language development, serum APPs, serum IGF-1, ferritin and hemoglobin, whole EFA blood concentrations and reported morbidity among children 6-23 months old with MAM in Burkina Faso.
- To compare the effectiveness of different soy qualities (dehulled soy versus soy isolate) and different amounts of protein provided by dry skimmed milk (DSM) on the outcomes among 6-23 months old children with MAM in Burkina Faso.
- To explore childcare practices related to supplementary feeding as well as the adherence to and acceptability of the food supplements.

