### 3.1.5. Outcomes and adverse events

#### **Efficacy**

- Primary outcome: absolute lean-mass increment (in kg) from baseline at 3 months using deuterium dilution technique.
- Secondary outcomes lean-mass increments in kg/cm and in g/kg/day, increase of WHZ to >-2, linear growth, MUAC, level of physical activity, development in motor and language milestones, thymic size, morbidity (e.g. malaria, severe anemia, severe acute malnutrition, diarrhea, respiratory infection, hospitalization, death), hemoglobin concentration, serum acute phase proteins, IGF-1, serum ferritin and whole blood concentrations of essential fatty acids.

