### *3.1.7. Sample size*

In the absence of information on the increase of LBM from 0-3 months among children with MAM in this age group, we assume that a 0.4 SD difference in change/increase in lean body mass between groups as clinically relevant. The sample size per group,  $n$ , required to detect a change,  $d$ , in a continuous variable with standard deviation,  $s$ , with alpha set at 5% and a 80% power, is  $16*s^2/d^2$ . Hence, to detect a 0.4 SD greater increase in lean body mass between 2 products/cells, we will need 100 children in each group. To allow for a 25% expected loss to follow-up/drop-out in the nutritional program in Burkina Faso, we will include 134 children in each of the 12 intervention groups (cells) then  $12 \times 134 = 1608$  children.

Considering a recruitment rate of 54 children with MAM per month per CSPA, the recruitment is therefore expected to last about 6 months and will be limited five CSPA (i.e., 54 children with MAM \* 6 months \* 5 CSPA = 1620 children).

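### The secondary objective asks for gains in weight-for-height and MUAC, but both outcome lists give WHZ only as a cut-off crossing, which some children may have passed at entry; MUAC has a cut-off in one list only

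*Combined protocol and SAP*

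**What the plan says.** Section 2.2 (Secondary objectives) asks for the effect of three months of supplementation "on weight-for-height increase, increase in MUAC, linear growth, thymic size" and further outcomes. No cut-off is attached to weight-for-height or to MUAC.

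The Summary (Outcomes) lists "increase of WHZ to >-2, linear growth, increase in MUAC > 125 mm". Section 3.1.5 (Efficacy) lists "increase of WHZ to >-2, linear growth, MUAC, level of physical activity". WHZ is therefore a crossing of -2 in both lists, while MUAC carries 125 mm in the Summary and no cut-off in section 3.1.5.

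Section 3.1.13 describes a linear mixed model for change in lean mass, with WHZ and MUAC among its covariates. It classes all analyses of secondary endpoints as secondary, without multiplicity adjustment. It does not say whether WHZ and MUAC are analysed as continuous or binary, and it names no model for a binary outcome.

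Entry (Summary, Participants; section 3.1.2) is by WHZ from -3 to below -2, or by MUAC from 115 mm to below 125 mm.

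**The concern.** An objective about how much children gain is matched, for WHZ, only with an outcome about who crosses a line. On that outcome a child who goes from -2.9 to -2.1 counts the same as one who does not gain, and a child who goes from -2.1 to -1.9 is a success.

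The either/or entry rule makes this more than a matter of wording. A child admitted on MUAC alone can start with WHZ already above -2, and a child admitted on WHZ alone can start with MUAC already above 125 mm. The lists give no denominator, so it is unclear whether such children count as successes, as failures or not at all.

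For MUAC, the reported result depends on which list the analyst follows, and the analysis section does not settle it.

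**Working it through.** **1. The passages side by side**

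| Place | WHZ | MUAC |
|---|---|---|
| Section 2.2, secondary objective | gain, no cut-off | gain, no cut-off |
| Summary, Outcomes | crossing -2 | 125 mm attached |
| Section 3.1.5 | crossing -2 | no cut-off |
| Section 3.1.13 | form not stated | form not stated |

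The cut-off itself also varies. The outcome lists require WHZ above -2, while the recovery footnote in the Summary and the referral rule in section 3.1.3 use -2 or above.

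**2. Who can be scored.** By route of entry:

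- Both criteria met: both crossings are defined.
- MUAC only: WHZ is already -2 or higher at baseline.
- WHZ only: MUAC is already 125 mm or more at baseline.

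The documents do not give the size of the last two groups. Change from baseline is defined in all three.

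**3. The plan's own figure.** Section 3.1.7 works "with alpha set at 5% and a 80% power" and states that "to detect a 0.4 SD greater increase in lean body mass between 2 products/cells, we will need 100 children in each group". Check: 16/0.4² = 100. With 25% loss, 100/0.75 = 133.3, so 134; 12 × 134 = 1608. This reproduces. The multiplier 16 is about 2 × (1.96 + 0.84)², so the test is two-sided. Power at 100 per cell is Φ(0.4/√(2/100) - 1.96) = Φ(2.828 - 1.96) = 0.807.

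**4. The same shift, cut at a threshold.** Two inputs are assumptions. The 0.4 SD is borrowed from lean mass, because the documents give no effect size or SD for WHZ or MUAC. The share p1 of the lower group that crosses is not given either, so a range is shown.

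- p2 = Φ(Φ⁻¹(p1) + 0.4)
- SE = √([p1(1 - p1) + p2(1 - p2)]/n)
- power = Φ((p2 - p1)/SE - 1.96)

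Example with p1 = 0.50 and n = 100: p2 = Φ(0.4) = 0.655; SE = √((0.250 + 0.226)/100) = 0.069; (0.655 - 0.500)/0.069 = 2.25; power = Φ(0.29) = 0.62.

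Section 3.1.13 merges two cells per milk level and three per soy type within each arm for lean mass, giving about 200 and 300 completers per group.

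| Lower group crossing | Other group | 100 v 100 | 200 v 200 (milk) | 300 v 300 (soy) |
|---|---|---|---|---|
| 20% | 33% | 55% | 84% | 95% |
| 30% | 45% | 60% | 88% | 97% |
| 40% | 56% | 62% | 89% | 98% |
| 50% | 66% | 62% | 89% | 97% |
| 60% | 74% | 59% | 87% | 97% |
| 70% | 82% | 54% | 83% | 94% |
| 80% | 89% | 45% | 74% | 89% |
| Continuous, 0.4 SD | | 81% | 98% | >99% |

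**5. Sensitivity**

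- Outside this band, single-cell power is 44% at 10% crossing and 31% at 90%.
- A pooled-variance test lowers the single-cell figures by about one point.
- A cut on WHZ acts on the final value, not on the change. With baseline WHZ uniform from -3 to -2, an SD of change of 0.4 to 1.0 and a mean gain of 0.2 to 1.0 (all assumed), single-cell threshold power is 30-58%.
- The smaller loss in merged groups is largely saturation. At effects that give about 80% continuous power (0.28 SD at 200, 0.23 SD at 300), threshold power for 20-80% crossing is again about 46-61%.

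**The case against.** The strongest reply is that the WHZ threshold is deliberate. Section 1.3 describes recovery past a weight-for-height cut-off as the usual outcome of earlier studies and warns that weight gain alone may only reflect fat, which is why lean mass is primary. An objective worded generally and then made concrete as a crossing is ordinary drafting, and WHZ is the same in both outcome lists. For MUAC, section 3.1.5 agrees with the objective, and only one loosely worded phrase in the Summary departs from it. This stands as a reason to keep the recovery proportions as secondary outcomes. It does not supply an outcome for the gain named in the objective, nor a denominator for children already past a cut-off.

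The second reply is that the power figures are not the trial's. That also stands. The 0.4 SD belongs to lean mass, the crossing shares are assumed, the trial is not powered on these endpoints, and the merged comparisons lose less. A binary analysis can adjust for baseline too.

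A reader might infer that the measurements exist at every visit and that the threshold discards all of them. That is too strong for WHZ: section 3.1.11 has height measured only monthly during the intervention. The fix needs only the baseline and 3-month values, which are scheduled.

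**Conclusion.** The mismatch is real and worth correcting. The WHZ outcome as listed answers the stated objective poorly, is undefined or already met at baseline for children who entered on MUAC alone with WHZ above -2, and has no stated analysis. MUAC is defined differently in the two lists, and a 125 mm crossing has the same baseline problem for children who entered on WHZ alone.

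The information loss is illustrative. At a borrowed 0.4 SD with 20-80% of the lower group crossing, power goes from about 81% to about 45-62% for single cells, from about 98% to 74-89% for merged milk groups, and from above 99% to 89-98% for merged soy groups.

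A reader might infer that the trial is undersized, or that the fall to 45-62% is a property of this trial. The documents support neither. The stated sample size reproduces and concerns lean mass only, and no effect size or crossing share is given for WHZ or MUAC. Nor do they support treating the recovery threshold as a mistake.

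**What to change.** - In the Summary (Outcomes) and section 3.1.5, add change from baseline to 3 months in WHZ and in MUAC (mm) as secondary outcomes. In section 3.1.13, state that they are analysed in the planned linear mixed model with adjustment for the baseline value.
- Keep the threshold-crossing proportions as secondary outcomes beside them, computed among children below the relevant cut-off at baseline, and name the binary analysis.
- Use the same wording in the Summary, section 2.2 and section 3.1.5. Reconcile the strict WHZ cut-off in the outcome lists with the inclusive one in the Summary footnote and section 3.1.3.

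No new child, visit or measurement is needed. The cost is a little more analysis and two more secondary results without multiplicity adjustment.

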### Follow-up chart of the participants

| Time (months)                                                                                                                          | 0       | 1 | 2 | 3 | 4 | 5 | 6 |
|----------------------------------------------------------------------------------------------------------------------------------------|---------|---|---|---|---|---|---|
| Fortnightly visits                                                                                                                     | X       | X | X | X | X | X | X |
| Screening for eligibility, recruitment, consent, randomization, baseline questionnaire (socio-demographic and medical characteristics) | ○       |   |   |   |   |   |   |
| Food supplementation (LNS & iCSBS arms)                                                                                                | ←-----→ |   |   |   |   |   |   |
| Education on nutrition, hygiene and health                                                                                             | ○       | ○ | ○ | ○ |   |   |   |
| Regular visits (clinical examination; morbidity, adverse events, and adherence questionnaire)                                          | ○       | ○ | ○ | ○ | ○ | ○ | ○ |
| Weight, MUAC, skinfolds, knee-heel length                                                                                              | ○       | ○ | ○ | ○ | ○ | ○ | ○ |
| Height, crown-rump length                                                                                                              | ○       | ○ | ○ | ○ | ○ | ○ | ○ |
| Blood sampling                                                                                                                         | ●       |   |   | ● |   |   | ● |
| Lean Body Mass (deuterium dilution test)                                                                                               | ○       |   |   | ○ |   |   |   |
| Physical activity                                                                                                                      | ○       |   |   | ○ |   |   | ○ |
| Child development (motor and language milestones)                                                                                      | ○       |   |   | ○ |   |   | ○ |
| Acceptability questionnaire                                                                                                            |         | ○ |   | ○ |   |   |   |
| Diet questionnaire                                                                                                                     | ○       |   |   | ○ |   |   | ○ |
| Thymic size (Ultrasound)                                                                                                               | ○       |   |   | ○ |   |   | ○ |

# 1. Introduction

## 1.1. Background

Acute child malnutrition (wasting) is a major global health problem, resulting in considerable morbidity and mortality. Children surviving from malnutrition may grow up with impaired intellectual and working capacity (*Black RE et al, 2008*). It has been estimated that more than 19 million children worldwide suffer from severe acute malnutrition (SAM, defined by a weight-for-height  $< -3$  z-scores), and, in addition, more than 36 million (*Black RE et al, 2008*) from moderate acute malnutrition (MAM, defined by a weight-for-height between  $-3$  and  $-2$  z-scores), which may progress to SAM.

Research has advanced the treatment of SAM, and significantly reduced its case fatality due to improved management protocols (*Manary et al, 2008*) using special milk based formulas (F-75 and F-100) and lipid-based Ready to Use Therapeutic Foods (RUTFs). In contrast to SAM, the management of MAM has only recently started to get more attention. Children with MAM have typically been given fortified blended flours (FBF) made by mixing soy and maize flours with added vitamins and minerals, such as corn-soy blend (CSB). The impact of this approach has been regularly questioned over the last 30 years (*Beaton GH et al, 1982; Navarro-Colorado C, 2007*). Until recently, their apparent lack of impact has been attributed to programmatic factors, such as food sharing, or the effect of repeated infections limiting the impact of food supplementation. These limitations have been challenged by the success of treating and preventing MAM with RUTF in conditions where the same programmatic difficulties applied (*Defourny I et al, 2007; Isanaka S et al, 2009; Nackers F et al, 2010*).

FBF were designed more than 30 years ago, at a time where an insufficient protein intake was perceived as *the* major problem in child nutrition in low-income countries (*Prentice AM, 2005; McLaren DS et al, 1982*). As a result, they have a higher proportion of energy derived from proteins than foods currently used to treat SAM (F100 and RUTF), which may be unnecessary and may decrease appetite (*Halton TL et al, 2004*). This high level of protein is often obtained by the inclusion of unrefined soy flour, which contains high levels of antinutrients, including phytates, that inhibit the absorption of key minerals needed for recovery, in particular zinc (*Erdman et al, 2004*). In addition to containing too much protein, FBFs have also been criticized because they do not contain animal-source protein (*Webb 2011*). Moreover, a large proportion of the phosphorus provided by soy flour is also provided by phytates and, as such, is not biologically available (*Golden M, 2008*). In addition, soy

---

 Numbers are based on analysis of 388 national surveys from 139 countries carried out in 2005 and according to the new WHO growth standards (Black et al 2008).

flours may result in high levels of unabsorbed carbohydrates, which may provoke flatulence and decrease the acceptability of soy containing products (*Suarez et al, 2009*). Another problem is that they do not meet nutritional needs of young children (*Chaparro and Dewey 2010*). Limitations of the formulation of the traditional CSB for the management of MAM have increasingly been recognized in recent years (*[name] et al, 2009; WFP 2008*). Several organizations have started developing and testing new products for the treatment of MAM, either in the form of improved FBFs, such as CSB+ and CSB++ produced by WFP or lipid based products (based on RUTFs used for SAM treatment) called lipid based nutrient supplements (LNS) or Ready to Use Supplementary Foods (RUSF). For the purpose of this protocol, LNS will be used.

The interest in LNS for the management of MAM is a result of demonstrated success of RUTF for MAM management (*Defourny I et al, 2007*) and prevention (*Isanaka S et al, 2009*). While RUTFs appeared to be a good product for treating MAM it is also an expensive product and its price prevents the use beyond small-scale projects. Formulation of similar products, based on less expensive ingredients and given in smaller amounts, grouped under the generic term of lipid-based nutritional supplements (LNS) therefore seemed to be an attractive option. Promising results in terms of their acceptability (*Adu-Afarwuah S et al, 2010; Hess S et al, 2010*), effect on growth (*Adu-Afarwuah S et al, 2007; Phuka et al 2008; Phuka et al 2009*) and weight gain (*Thakwalakwa c et al, 2010; Matilsky et al, 2009*) have already been demonstrated. They have also been shown to be more effective than CSB (*Matilsky et al, 2009*) and micronutrient supplements (sprinkles and nutritabs) (*Adu Afarwuah et al, 2007*). The higher quality CSBs may however be an alternative to LNS. One recent study has shown that CSB++ was not inferior to LNS in terms of recovery from MAM (*LaGrone et al, 2012*).

Some key factors contributing to the effectiveness of RUTF also characterize LNS, in particular:

- Their convenience of use: LNS can be eaten as a snack, without preparation, or added to family foods. LNS should not be mixed with water and are delivered in individual sealed packages preventing bacterial contamination.
- Their high fat content, including high levels of essential fatty acids: this may explain their efficacy, as low essential fatty acid intakes, especially of the n-3 family, have been reported to limit growth of children in some African countries (*Rocquelin G et al, 2003*).
- Their content of dairy products: milk apparently contains growth factors, which may be interesting, particularly in children with associated stunting (low height for age) (*Hoppe C*

*et al, 2008*); also, dairy products provide highly available phosphorus, and they are free of anti-nutrients.

There is a need to disentangle which factor is really important in RUTF to promote rapid catch-up growth, as each of these factors has different cost implications if formulated within a LNS or CSB. In particular, milk appears to be important during nutritional rehabilitation and is now added to an improved CSB, CSB++ (currently known as Supercereal+), designed for the use in small children. The addition of milk to CSB++ may also be responsible for the early successes of CSB++ (see above). Milk is however an expensive ingredient and the amount needed is unknown (*[name] KF et al, 2009*). For example, adding 10- 15% milk powder to a FBF would double its price (*Hoppe C et al, 2008*). It is therefore important to identify whether milk is really necessary in both CSB and LNS products and if yes, how much milk is needed to achieve the best balance between effect (benefits in terms of functional outcomes in children with MAM) and price, *i.e.* the milk content that optimizes the cost-effectiveness of the product.

It is also possible to lower the anti-nutrient content of FBF by using soy protein extracts, instead of unrefined soy flours, to improve their impact. Soy protein extracts are used successfully in rich countries to prepare soy based infant formula with an efficacy to promote growth comparable to that of milk based infant formula (*Agostoni C et al, 2006*). Soy protein extracts could be a less expensive alternative solution as an ingredient in LNS or improved FBF. However, there is uncertainty about the efficacy of using plant protein isolates as a less expensive substitute for dairy products.

Existing formulations of LNS products for the treatment of MAM are varying in terms of composition. Some products are containing milk (Eezee RUSF from GC Rieber Compact A/S) while in others, milk is replaced by whey (PlumpySup from Nutriset) and only in negligible amounts. Furthermore the quality of soy is also varying in the different existing LNS used for the treatment of MAM today. Indeed, adding more milk than necessary will increase the cost of the product, and prevent some children from getting access to treatment.

It is therefore important to explore the different options in terms of quantity of milk and quality of soy needed for the treatment of MAM, both for LNS and FBFs, and compare their respective effectiveness and cost implications.

Although their nutritional value is the first consideration, the newly developed food supplements should also be consistent with cultural contexts. Providing food aid that is culturally appropriate to recipients and that can be used efficiently at household level is of

primary importance (*The sphere project*). The effectiveness of the supplementary products will depend, among other things, on its acceptability, adherence and the way the products are perceived and managed within the household, and these factors are therefore critical for future project implementation (*Santon IS et al, 2005; Flax VL et al, 2009; Adu-Afarwah S et al, 2008; Rowe JP 2008*). Furthermore, child survival, growth and development depend not only on food intake, but on multiple direct and indirect factors as described in UNICEF's conceptual framework of malnutrition (*UNICEF 1990*). As an example, the amount of food a child consumes is not only determined by the amount and quality offered, but also on the behavior of the caregiver (*Bentley MB et al, 1991*), and child care practices related to feeding are important determinants for dietary intake and ultimately child growth. A well planned approach based on an understanding of the context is crucial prior to program planning and implementation, and may lead to better and more effective provision of nutrient supplementation programs. Therefore, this study will also focus on childcare practices related to supplementary feeding as well as perceptions, acceptability of and adherence to new and improved diets.

